### Statistical analysis

Data will be analyzed on an intention-to-treat basis at the 12-week (post-testing) timepoint. The primary outcome measure is binary - using or not using glucose-lowering medication at 12 weeks - and data will be analyzed by logistic regression, with the stratified allocation factors included as fixed effects together with trial arm and sex. We will derive the odds ratio for use of glucose-lowering medication, and odds will be converted to predicted probabilities (risk differences). Participants who fail to complete the intervention or are lost to follow up from the Pharm-TCR group will be retained in the analyses and will be considered as not achieving the primary outcome. The secondary outcome measures of anthropometrics, blood pressure, medication dose changes, quality of life, and all blood measures will be analyzed using constrained baseline longitudinal data analysis via a linear mixed model [25]. This approach provides a principled method for addressing missing data, including missing baseline data as baseline values are part of the response vector in this model. In addition, study site will be included as a random effect in the linear mixed models to account for site variability in the outcome measures [26]. Model specification will be examined by visual inspection of residuals plots, with appropriate data transformations used if indicated. For the primary endpoint we shall report the odds ratios and predicted probabilities (risk differences) with 95% confidence intervals. Secondary continuous outcomes will be reported as mean differences with 95% confidence intervals. Whenever possible, data analysis will be performed blinded to the allocations.

It is not anticipated that any participants in the TAU group will discontinue glucose-lowering medications; however, to be conservative, the sample size was calculated based on an expected proportion of medication use of 80% in the TAU group and a 20% difference in the proportion of participants on glucose-lowering medications at 12 weeks in the Pharm-TCR group. A sample size of 100 per group provides 80% power to detect a 20% difference in the proportion of patients on glucose-lowering medications, accounting for 20% attrition with a two-sided *P* value of 0.05 (PASS 14 Power Analysis and Sample Size Software, 2015. NCSS, LLC. Kaysville, Utah, USA; ncss.com/software/pass).

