## Methods/design

A community-based randomized controlled trial that is pragmatic in nature, following a parallel-group design will be conducted. Patients with T2D (*N* = 200) will be recruited from across 12 pharmacy locations in the province of British Columbia, Canada. The pharmacists will use a secure password-protected website maintained by the University of British Columbia (UBC) Centre for Health Evaluation and Outcome Sciences (CHEOS) to implement the random allocation sequence. The secure website provides allocation concealment until the interventions are assigned. The allocation sequence generated was by a researcher from CHEOS using PROC PLAN in SAS 6.4 software. Participants will be stratified by site (pharmacy) and glucose-lowering medications (two or fewer, three or more (or taking exogenous insulin)) and randomized in a 1:1 allocation ratio using permuted block sizes, to either the therapeutic nutrition group or the treatment-as-usual (TAU) group. Due to the nature of the interventions and the involvement required of the pharmacists, they cannot be blinded to final treatment allocations of the participants. The protocol was approved by the University of British Columbia Clinical Research Ethics Board (H16–01539) and the trial was registered on ClinicalTrials.gov (NCT03181165) on 8 June 2017. A flow diagram of the trial is presented in Fig. 1. Additional file 3 contains the SPIRIT 2013 Checklist.

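### If no TAU participant stops medication, as the protocol expects, the planned primary odds ratio has no finite maximum-likelihood estimate or two-sided 95% CI, and no fitting method is named for that case

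*Protocol article*

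**What the plan says.** All of this is in the Statistical analysis section of the protocol article unless noted.

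- Primary model: "data will be analyzed by logistic regression, with the stratified allocation factors included as fixed effects together with trial arm and sex". Under Methods/design, allocation is stratified by pharmacy and by a two-level medication stratum, and patients are "recruited from across 12 pharmacy locations in the province of British Columbia, Canada". The model therefore holds arm, sex, medication stratum and 11 site indicators.
- Reporting: "For the primary endpoint we shall report the odds ratios and predicted probabilities (risk differences) with 95% confidence intervals".
- Expectation for the control arm: "It is not anticipated that any participants in the TAU group will discontinue glucose-lowering medications".
- Sample size: the text goes on that "to be conservative, the sample size was calculated based on an expected proportion of medication use of 80% in the TAU group", with "a 20% difference in the proportion of participants on glucose-lowering medications at 12 weeks in the Pharm-TCR group". It concludes that "A sample size of 100 per group provides 80% power to detect a 20% difference", allowing for 20% attrition at two-sided 0.05.

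The inclusion criteria require at least one glucose-lowering drug at entry. The stated expectation is therefore that every TAU participant is still a user at week 12. The section names no estimation method beyond logistic regression, no type of test or interval, and no alternative for an empty cell.

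**The concern.** Two statements in one section do not fit together. One promises an odds ratio with a 95% interval from a logistic regression. The other forecasts a result for which a standard fit of that regression has no finite odds ratio. With no stoppers in TAU, the likelihood keeps rising as the arm coefficient grows, so the fit runs off to infinity and stops wherever the software's iteration limit lies.

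Two things are at stake. First, default Wald output would show a decisive success as non-significant, with a meaningless odds ratio. Second, the remedy would have to be chosen after the arm-level counts were known. The section promises blinded analysis only where possible, so that choice could not be shown to be independent of the result.

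**Working it through.** **Inputs from the protocol article.** 100 per arm, 20% attrition, 12 sites, 80% v 60% on medication for sample size, and no TAU stoppers expected. The article gives no Pharm-TCR stopping rate to go with zero in TAU, so 20% and 40% are assumed below to show a range.

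**1. The plan's own figure.** With p1 = 0.8, p2 = 0.6 and mean 0.7, the pooled formula is n = [1.96·√(2·0.7·0.3) + 0.842·√(0.8·0.2 + 0.6·0.4)]² / 0.2² = 82 per arm after rounding up, and 82/0.8 = 103. The unpooled formula gives 79, and 79/0.8 = 99. Power at 80 per arm is 0.794 (pooled) or 0.807 (unpooled). The stated 100 per group and 80% power are reproduced.

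**2. How likely zero TAU stoppers is.** P(zero) = (1 − p)^n, where n = 80 applies if 20% of TAU outcomes are missing and not imputed.

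| True TAU stopping rate | n = 100 | n = 80 |
|---|---|---|
| 0% (the stated expectation) | 100% | 100% |
| 1% | 37% | 45% |
| 2% | 13% | 20% |
| 5% | 0.6% | 1.7% |
| 20% (sample-size rate) | 2 × 10⁻¹⁰ | 2 × 10⁻⁸ |

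**3. The maximum-likelihood fit with a zero cell.** Arm-only model, 20/100 v 0/100 stopping, Newton-Raphson:

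| Iteration | Log odds ratio | SE | Wald p |
|---|---|---|---|
| 8 | 7.8 | 10 | 0.43 |
| 12 | 11.8 | 74 | 0.87 |
| 16 | 15.8 | 544 | 0.98 |
| 20 | 19.8 | 4019 | 0.996 |

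The coefficient gains 1 per iteration without limit. At 40/100 v 0/100 the pattern is the same. With one TAU stopper (20 v 1) the arm-only model converges: log odds ratio 3.21, SE 1.04, Wald p = 0.002.

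**4. What still exists with zero TAU stoppers.** The likelihood-ratio statistic is 2(l₁ − l₀). At 20/100 v 0/100, l₁ = 20 ln 0.2 + 80 ln 0.8 = −50.04 and l₀ = 20 ln 0.1 + 180 ln 0.9 = −65.02. The statistic is 29.95, p = 4 × 10⁻⁸. At 40/100 it is 65.56, p = 6 × 10⁻¹⁶. Inverting the profile likelihood bounds the odds ratio for stopping at 12.2 or more (20/100) or 33.1 or more (40/100), open above. For medication use that is 0.082 or less, or 0.030 or less.

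**5. Full model.** Arm, sex, medication stratum and 12 sites; 300 simulated trials per row; 200 patients spread at random over sites, strata and sex.

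| Pharm-TCR v TAU stopping | Zero TAU stoppers | Wald p < 0.05 | Likelihood-ratio p < 0.05 |
|---|---|---|---|
| 20% v 0% | 100% | 0% | 100% |
| 40% v 0% | 100% | 0% | 100% |
| 40% v 1% | 33% | 67% | 100% |
| 40% v 2% | 13% | 86% | 100% |
| 40% v 20% (planning rates) | 0% | 85% | 85% |

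**6. Risk difference.** At 20/100 v 0/100 the estimate is 20 points. A delta-method interval gives the TAU arm no variance at the limit: 20 ± 1.96·√(0.2·0.8/100) = 12.2 to 27.8. Newcombe gives 12.4 to 28.9. At 40/100 the figures are 30.4 to 49.6 and 30.2 to 49.8. The numerical gap is modest in these unadjusted tables, but the delta method treats the TAU rate as known to be zero and works from a covariance matrix that has diverged.

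**7. The remedy.** For a 2×2 table Firth's estimate equals adding 0.5 to each cell. At 20/100 v 0/100 this is (20.5/80.5)/(0.5/100.5) = 51.2. A Wald-type interval, with SE = √(1/20.5 + 1/80.5 + 1/0.5 + 1/100.5) = 1.44, is 3.0 to 859. The profile interval from the penalised log-likelihood, l + ½ ln|I|, cut at 3.84/2 below its maximum, is 6.9 to about 6,500, with penalised likelihood-ratio p = 3 × 10⁻⁷. Both are finite but very wide, and they differ enough that the type must be named.

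**The case against.** Five points stand on the other side.

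- **The test survives.** A reader might infer that the model cannot be estimated at all, or that there would be no p-value. The documents do not support that. The likelihood-ratio p-value comes from the same planned model and is very small. A one-sided bound on the odds ratio exists, and the risk difference, which is also promised, is finite.
- **Wald is not in the plan.** The section says only logistic regression. Wald tests and delta-method intervals are common software defaults, not commitments. Firth and exact fits are also logistic regression.
- **It needs one exact count.** A single TAU stopper makes the arm-only model estimable. The authors also planned on 80% use in TAU, so they allowed for some stopping. That allowance served the sample size and did not alter the analysis.
- **A statistical analysis plan may cover it.** Only a condensed article is shown, and test and interval types are usually left to the fuller document. This weakens any complaint about missing detail. It does not remove the conflict, because the article itself fixes the model, the covariates and the estimates, and itself forecasts the result that defeats one of them.
- **The site terms are not the cause.** A reader might infer that pharmacies with no variation in outcome also make the arm effect inestimable. They do not: such a site sends only its own indicator to infinity and drops out of the information on arm. In 600 simulated trials at planning rates with assumed unequal site sizes, 62% had such a site. In those trials the arm SE stayed between 0.31 and 0.44, and estimate and SE matched the fit without those sites to about 10⁻¹⁰.

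**Conclusion.** The point holds in a limited, conditional form. If exactly zero TAU participants stop medication, the promised odds ratio has no finite maximum-likelihood estimate and no two-sided 95% interval, default Wald output is invalid, and a delta-method interval for the risk difference is unreliable. The evidence of an effect would not be lost.

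The probability depends wholly on the true TAU stopping rate. It is certain at the stated expectation of zero, about 1 in 3 at 1%, about 1 in 8 at 2% (n = 100), and negligible at 20%. The article's account of usual care, in which adjustment is typically an increase in drugs or dose, makes a rate near zero plausible.

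The assumptions are Pharm-TCR stopping rates of 20% and 40%, patients spread at random over sites and strata, and 100 analysed per arm except where 80 is shown. The algebraic result in step 3 needs none of these beyond an empty TAU cell and at least one Pharm-TCR stopper.

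**What to change.** Before unblinding, add to the Statistical analysis section (or confirm that the analysis plan already states):

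1. The primary logistic model, with the same covariates, is fitted by Firth penalised likelihood, whatever the counts. The odds ratio has a profile penalised-likelihood 95% interval, and the test is the penalised likelihood-ratio test. An exact or Cochran-Mantel-Haenszel test would also serve, but one must be named.
2. The risk difference is reported with a stratified interval that stays valid with a zero cell, such as Newcombe or Miettinen-Nurminen, with the strata and weights named.

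This takes two or three sentences and no new data. The cost is slight shrinkage of the odds ratio. With an empty cell its upper limit will also be very large, so the risk difference will be the more readable result. Replacing the fixed site terms is optional and not needed for this repair.

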### Trial procedures

Eligible participants who enroll in the study will undergo baseline assessment of medications and A1C, fasting glucose, triglycerides, liver ALT, AST, GGT, serum triglycerides, HDL and LDL cholesterol, and high sensitivity (hs)-C-reactive protein (hs-CRP). Weight, height, BMI, body fat percentage (measured by bioelectrical impedance), and waist circumference will be taken as anthropometric measurements, and quality of life will be assessed using the SF-20 questionnaire. Participants’ primary care physicians will be notified of all laboratory results as per typical blood requisition (by fax). Participants will fill out a 3-day diet record to assess habitual food intake and the Godin Leisure-Time Exercise Questionnaire to assess typical physical activity. Participants will also be asked to fill out a questionnaire regarding their ethnicity and socioeconomic status. Following the baseline assessments, participants are randomized to either the Pharm-TCR diet group or the TAU control group. A simplified cost-effectiveness analysis including the cost of medications and cost of the foods and pharmacists’ time during the intervention will be conducted as an exploratory outcome.

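### Baseline A1C is measured before randomisation but is not in the primary logistic model; adding it, with site as a random intercept, is a small and almost free improvement

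*Protocol article*

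**What the plan says.** The primary outcome is binary, "using or not using glucose-lowering medication at 12 weeks". The Statistical analysis section names the covariates of its logistic model: trial arm and sex, "with the stratified allocation factors included as fixed effects together with trial arm and sex". Methods/design defines those factors: "Participants will be stratified by site (pharmacy) and glucose-lowering medications (two or fewer, three or more (or taking exogenous insulin". Patients "will be recruited from across 12 pharmacy locations in the province of British Columbia, Canada", so site as a categorical fixed effect means 11 indicator terms (inferred; the article does not give that count).

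Trial procedures says that participants "will undergo baseline assessment of medications and A1C, fasting glucose" and other markers, and that randomisation follows. Baseline A1C is therefore available for adjustment.

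For the secondary outcomes, "study site will be included as a random effect in the linear mixed models". On reporting: "For the primary endpoint we shall report the odds ratios and predicted probabilities (risk differences) with 95% confidence intervals".

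**The concern.** The covariate list is a stated choice, so this is not detail left to an analysis plan. Three parts of the article link A1C to the outcome. Background describes adding agents until the A1C target is met. The treatment-as-usual section says that dose or number of drugs typically rises when A1C is not below 7.0%. The Discussion repeats that logic. A participant's starting A1C is thus a natural predictor of whether drugs can be stopped by week 12.

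Adjusting for such a variable can raise power and tighten the risk difference at no cost to patients. It also guards against chance imbalance in A1C, on which randomisation is not stratified. That matters here because the Discussion and Conclusion judge success by stopping drugs without worsening glycaemia.

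The way site enters is a second, related matter: 11 indicators in a binary model with few events can disturb the test and leave some coefficients without a finite estimate.

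**Working it through.** **1. The plan's own figure.** Inputs from Statistical analysis: 80% v 60% on medication, two-sided 0.05, 80% power, 20% attrition.

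n = [1.96·√(2·0.7·0.3) + 0.8416·√(0.8·0.2 + 0.6·0.4)]² / 0.2² = (1.2702 + 0.5323)² / 0.04 = 81.2, so 82 per arm.

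Allowing for attrition: 82/0.8 = 102.5 (103), or 82 × 1.2 = 98.4 (99). The stated 100 lies between. Power with 80 evaluable per arm is 79.4%. This is an unadjusted two-proportion calculation, so the covariate list does not affect it.

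**2. Model load.** With 80 evaluable per arm, non-use events are 80 × 0.20 + 80 × 0.40 = 48. The planned model has 11 site terms, stratum, sex, arm and intercept, 15 in all: 48/15 = 3.2 events per parameter. With a random site intercept plus A1C there are 5 fixed coefficients and one variance: 48/6 = 8.

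**3. Gain from A1C.** The simulation used 160 evaluable, 12 sites, permuted blocks within site and stratum, 80% v 60% on medication, and 6,000 runs per row. Assumptions, none from the documents: stratum log odds ratio 0.5, site SD 0.3, half of participants in the upper stratum and 60% of those on insulin. Log odds ratios per SD of A1C / for insulin were 0.3/0.4 (weak), 0.5/0.7 (moderate) and 1.0/1.5 (strong). RD is the risk difference.

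| Prognosis | Power: planned → + A1C | SD of RD | Fall in SD | SE of log OR | Power with insulin also added |
|---|---|---|---|---|---|
| Weak | 83.5% → 83.9% | 0.0697 → 0.0695 | 0.3% | 0.399 → 0.407 | 83.9% |
| Moderate | 84.1% → 85.3% | 0.0683 → 0.0673 | 1.5% | 0.402 → 0.420 | 85.7% |
| Strong | 85.7% → 89.5% | 0.0685 → 0.0646 | 5.7% | 0.414 → 0.469 | 90.3% |

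The Monte Carlo error of a single power figure is √(0.84 × 0.16/6000) = 0.5 points, so the weak-case gain is close to nothing. A further simulation of the same design gave about 1 to 2 points for weak to moderate prognosis and 3 to 4 if strong. Insulin on top of stratum and A1C adds 0 to 0.8 points.

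The SE of the log odds ratio rises, yet power rises too because the estimate moves further: in the moderate case 1.166/0.402 = 2.90 becomes 1.238/0.420 = 2.95.

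**4. Almost no stopping under TAU.** At 98% v 78% on medication (3,000 runs, moderate prognosis), power is 79.4% with and without A1C.

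**5. Site terms and precision.** In the moderate case, the SD of the risk difference is 0.0681 without site terms and 0.0683 with them. The further simulation gave 0.0700 and 0.0702.

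**6. Site terms and type I error** (30% off medication in both arms in the first two simulations).
- First simulation, 160 participants, 1,500 runs: 6.5% planned; 7.0% with A1C added and site still fixed; 5.5% without site terms but with A1C and insulin. Monte Carlo error is √(0.065 × 0.935/1500) = 0.6 points.
- Second, 2,500 runs: 6.0% (160 participants) and 6.6% (200) with site terms; 5.0% and 5.3% without them, unchanged when A1C is added.
- Third, 80 per arm: 5.9% with fixed site, 6.5% with A1C added, and 5.2% with site shrunk as a random effect, with or without A1C.

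**7. Sites without events.** Take 12 equal sites with no site variation. At 20% v 40% off medication and 160/24 = 6.67 per arm per site, the chance that a given site has no event is (0.8 × 0.6)^6.67 = 0.0075, so at least one such site occurs with probability 1 − 0.9925¹² = 9%. At 2% v 22% and 200/24 = 8.33 per arm per site, it is (0.98 × 0.78)^8.33 = 0.107, so 1 − 0.893¹² = 74%. With site variation added, simulation gave 81%.

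**The case against.** The strongest reply is that nothing here is wrong. Adjusting for the randomisation factors is standard and agrees with Methods/design, and an extra covariate is a preference. That stands, and it is why the point is minor. Random site in the secondary models is no contradiction either, since those are longitudinal linear models and the primary is a single-timepoint logistic regression.

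Readers might infer more than the documents support:
- **That insulin use is ignored.** It is not. The stratum is "glucose-lowering medications (two or fewer, three or more (or taking exogenous insulin", so every insulin user is in its upper level and that level is in the model. Only the split within that level is missing.
- **That 11 site terms give precision away.** Step 5 shows almost no cost. The case against them is error rate and estimability.
- **That the odds ratio becomes more precise.** Its SE rises. The gain is in power and the risk difference only.
- **That A1C is a proven predictor.** The article supports a link but gives no strength.

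A further caution concerns nominal power. In the moderate case the fixed-site planned model shows 84.1%, while the model without site terms but with A1C and insulin shows 83.7%. Part of the former comes from a slightly liberal test. Like for like, without site terms, the move is from 82.4% to 83.7%. Adding A1C while keeping site fixed would not cure the error-rate excess.

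Finally, a site without events does not by itself spoil the arm estimate, and a random intercept does not help if an entire arm has no events.

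**Conclusion.** The point holds as an optional, minor improvement. Baseline A1C is collected, tied to drug use by the protocol's own reasoning, and absent from the stated primary model.

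Under assumed prognostic strength, adding it is worth about 1 to 2 points of power and up to about 2% of the SD of the risk difference (weak to moderate), or 3 to 4 points and 5 to 6% (strong). The gain is nil if TAU stopping is near zero, and the article itself does not anticipate any TAU participant stopping.

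The change to random site rests on a mild type I error excess, seen in the same direction in three simulations but small against Monte Carlo error in each, and on sites without events, which matter mainly when stopping is rare. Absolute power levels depend on the 80-evaluable-per-arm basis; only differences between models are used here. A reader should not infer that the trial is underpowered because of this choice: the stated sample size is unaffected.

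**What to change.** In the Statistical analysis section, restate the primary model as a logistic regression with a random intercept for site and fixed effects for arm, medication stratum, sex and baseline A1C (continuous). Report the standardised (marginal) risk difference with its 95% confidence interval alongside the odds ratio, labelled as conditional on the covariates. Use simple mean imputation for a missing baseline A1C. A separate insulin indicator may be added, but little is lost without it.

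The cost is a sentence or two and no new data. The model must be fixed before unblinding. The conditional odds ratio will have a larger SE and a slightly different meaning from the one now planned.

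### The non-completion rule for the primary outcome covers Pharm-TCR only and makes no exception for an observed week-12 medication status, which biases the comparison against Pharm-TCR

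*Protocol article*

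**What the plan says.** All of this is in the Statistical analysis section of the protocol article, unless another section is named.

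- Analysis principle: "Data will be analyzed on an intention-to-treat basis at the 12-week (post-testing) timepoint".
- Primary outcome: binary, "using or not using glucose-lowering medication at 12 weeks". The Primary outcome section defines it by medication use alone, with no adherence condition.
- Rule for non-completion and loss: "Participants who fail to complete the intervention or are lost to follow up from the Pharm-TCR group will be retained in the analyses", and these participants "will be considered as not achieving the primary outcome".
- TAU: no rule is given for a participant whose week-12 status is missing. The mixed model presented as a way of handling missing data is for the secondary outcomes.
- Planning value for TAU: "expected proportion of medication use of 80% in the TAU group". The text also says "It is not anticipated that any participants in the TAU group will discontinue glucose-lowering medications", so the 80% is a deliberately cautious figure.
- Target effect: "a 20% difference in the proportion of participants on glucose-lowering medications at 12 weeks in the Pharm-TCR group", that is, 80% against 60%.
- Power: "A sample size of 100 per group provides 80% power to detect a 20% difference", two-sided 0.05, allowing for 20% attrition.

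**The concern.** The rule has two triggers joined by *or*. The second, loss to follow-up, concerns a missing outcome. The first, not completing the intervention, concerns adherence, and it applies whether or not week-12 status is known. Someone who stops the diet but is seen at week 12 off medication would, on the wording, be recorded as a failure. That is a different outcome from the one defined, and it is applied in one arm only.

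The rule also names only Pharm-TCR. Loss in the control arm is foreseen: the Treatment-as-usual control section offers the diet afterwards to help retain TAU participants. If missing TAU outcomes simply fall out of the logistic regression, one arm is analysed in full with failures filled in and the other as observed cases.

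At stake are the odds ratio and risk difference for the sole primary endpoint, and the power to detect a real effect.

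**Working it through.** **Inputs from the article.** 100 randomised per arm; 80% on medication in TAU and 60% in Pharm-TCR; 20% attrition; two-sided 0.05.

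**Assumptions not in the article.** Loss is equal in the two arms, d = 0.20 (10% and 30% also shown). The planning rates hold among those observed. Missing TAU participants are left out of the model.

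**Step 1: reproduce the stated power.** Pooled z-test, 80 evaluable per arm, mean rate 0.70:
- SE under the null = √(0.70 × 0.30 × 2/80) = 0.0725
- SE under the alternative = √((0.80 × 0.20 + 0.60 × 0.40)/80) = 0.0707
- power = Φ((0.20 − 1.96 × 0.0725)/0.0707) = Φ(0.82) = 79.4%

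The stated 80% is confirmed. This calculation treats attrition as lost sample size, not as failures filled in for one arm.

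**Step 2: rule as written.**
- Pharm-TCR on medication = 0.20 + 0.80 × 0.60 = 68%, n = 100
- TAU on medication = 80%, n = 80
- difference = 12 points; OR = (0.68/0.32)/(0.80/0.20) = 0.53; power about 44%

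**Step 3: same rule in both arms.**
- TAU on medication = 0.20 + 0.80 × 0.80 = 84%, n = 100
- difference = 84 − 68 = 16 points; OR = (0.68/0.32)/(0.84/0.16) = 0.40; power about 76%

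The part due to one-sidedness is d × (1 − TAU use) = 0.20 × 0.20 = 4 points.

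**Step 4: vary the loss, at 80% against 60%.**

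| Loss per arm | As written | Same rule in both arms |
|---|---|---|
| 10% | 16 points, power 69% | 18 points, power 82% |
| 20% | 12 points, power 44% | 16 points, power 76% |
| 30% | 8 points, power 22% | 14 points, power 68% |

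**Step 5: vary TAU use, with 20% loss and a 20-point effect among those observed.**

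| TAU use | As written | Same rule in both arms |
|---|---|---|
| 80% | 12.0 points, power 44% | 16.0 points, power 76% |
| 95% | 15.0 points, power 86% | 16.0 points, power 94% |
| 98% | 15.6 points, power 94% | 16.0 points, power 97–98% |

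At 100% TAU use the term d × (1 − TAU use) is zero.

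**Step 6: direction.** With no true effect (80% in both arms, 20% loss), the one-arm rule creates a difference of 0.20 + 0.80 × 0.80 − 0.80 = 4 points against Pharm-TCR. In 200,000 simulated trials the two-sided test rejected in 10.5%: 10.2% favoured TAU and 0.4% Pharm-TCR. With the same rule in both arms it rejected in about 5.2%.

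**Step 7: replacing an observed status.** If 20% of Pharm-TCR do not complete and a fraction q of them are observed off medication at week 12, use in that arm is overstated by 0.20 × q: 2 points at q = 10%, 8 points at q = 40%. The article gives no value for q. If these people belong to the 20% in Step 2, they are already scored as failures there, so this error is inside the 12-point figure and is not added to it.

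**The case against.** Several points can fairly be made for the plan.

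- **Intention to treat.** A reader might infer that the rule contradicts the intention-to-treat statement. The text does not support that: these participants stay in their randomised arm, and counting discontinuation as failure is a recognised composite strategy. What remains is that the article defines the outcome by medication use alone and applies the composite to one arm.
- **Known outcomes.** A reader might also infer that known outcomes will be overwritten on a large scale. This is not shown. The Pharm-TCR intervention section places the outcome assessment at the final weekly visit, which someone who stops would often miss. The weekly records give status before stopping, not at week 12. Still, a person who stops and attends week 12 is possible, and the wording makes no exception for them.
- **TAU.** The article does not say that TAU is analysed as observed cases; a full protocol or analysis plan may hold a TAU rule. Every asymmetry figure above depends on that assumption. But the concern is not only silence: a rule is stated, and it is stated for one arm.
- **Size.** The planning rate of 80% is the cautious value. At the near-complete TAU use the authors expect, the asymmetry is negligible. This stands, and it limits the size of the problem.
- **Direction.** The bias runs against Pharm-TCR and cannot produce a false claim of benefit. That also stands. It does not protect the effect estimates, which the plan undertakes to report with 95% confidence intervals.

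**Conclusion.** The concern holds in a limited form. The stated rule treats the arms differently and lets diet non-completion stand in for an observed outcome in Pharm-TCR. Both features bias the odds ratio and risk difference against Pharm-TCR.

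The loss of 4 of 16 points, and of power from about 76% to about 44%, is the result for the planning case only. It rests on 20% loss in each arm, 80% TAU use, and missing TAU participants being left out. It falls to 1 point at 95% TAU use and almost to nothing near 100%. The overstatement of 0.2q does not depend on the TAU rate, but q is unknown. The one-sided wording is certain; the size is not. This should be fixed before unblinding, but it does not threaten a false-positive finding for the intervention.

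**What to change.** Replace the sentence with a rule that applies to both arms:

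1. Use the observed week-12 medication status for every randomised participant who has one, whether or not the diet or the TAU period was completed.
2. Where week-12 status is unknown, count the participant as still using medication, identically in both arms.
3. Add one sensitivity analysis for unknown status, either multiple imputation or a tipping-point analysis.
4. If non-completion is meant to count as failure, label that a composite outcome and report it as secondary.

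The cost is a change of wording, minor analysis work, and some effort to obtain week-12 status from people who stop. One consequence should be accepted openly. If 20% of statuses are truly unknown in each arm, the symmetric rule gives about 76% power at the planning rates, not the stated 80%. Each status that is obtained reduces the number that must be filled in.
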